## Abstract

**Background:**

Lumbar disc herniation (LDH) is a common and frequently occurring disease in clinics. Low back pain and sciatica are the presenting symptoms of LDH. To some extent, it can be considered that measures with the capability to improve low back pain or sciatica have the potential to treat LDH. Ma’s bamboo-based medicinal moxibustion therapy can effectively reduce the degree of low back pain and has been widely used. Studies of small sample size have seen significant improvement on pain relief. The aim of this trial is to evaluate the clinical efficacy and safety of Ma’s bamboo-based medicinal moxibustion therapy in the treatment of LDH low back pain.

**Methods/design:**

The trial is a multicenter, randomized, parallel-group, non-inferiority study. Three hundred and twelve patients will be randomly assigned to a Ma’s bamboo-based medicinal moxibustion group (*n*=156) and an acupuncture group (*n*=156). Patients in each group will receive treatment every day, 6 times a week, 12 times in total. Follow-up will be conducted 14 days after treatment. The primary outcome will be the visual analog scale(VAS) at baseline, after 6 times of treatment, end of treatment, and follow-up. The secondary outcomes will include Oswestry disability indexes (ODI), modified Japanese Orthopaedic Association low back pain (M-JOA) score, serum β-endorphin (β-EP), and serum substance P (SP). β-EP and SP, as well as safety evaluation indexes (routine blood, liver, and kidney function and electrocardiogram), will be measure at baseline and after the end of treatment. The number, nature, and severity of adverse events will be recorded.

**Discussion:**

The results of the trial will compare the efficacy of low back pain in LDH between Ma’s bamboo-based medicinal moxibustion group and the acupuncture group and will be expected to make a systematic and objective evaluation of the clinical efficacy and safety of Ma’s bamboo-based medicinal moxibustion therapy.

**Trial registration:**

ChiCTR2000038725. Registered on 29 September 2020.

**Supplementary Information:**

The online version contains supplementary material available at 10.1186/s13063-022-06382-x.

## Background

Lumbar disc herniation (LDH) is a syndrome caused by the compression and stimulation of the lumbosacral nerve root and cauda equina nerve owing to the degeneration of the lumbar intervertebral disc, rupture of annulus fibrosus, and resulted nucleus pulposus protrusion. It occurs frequently in young and middle-aged individuals, with a higher incidence in males than females, among which L4/5 and L5/S1 are the vulnerable sites (>90%) [1]. Low back pain is the initial symptom of LDH, which is generally in the lumbosacral part, mostly soreness and swelling pain, which can radiate to the buttocks. It occurs repeatedly, aggravates after sitting, standing for a long time, or fatigue, and relieves after rest [2]. Clinically, low back pain may be induced by multiple factors. However, among patients with low back pain, outpatients and inpatients with LDH account for 10~15% and 25~40%, respectively [3]. There is a high incidence of LDH but a low rate of hospitalization. Most patients with LDH can be relieved after formal conservative treatment [4].

Low back pain and sciatica are the presenting symptoms of LDH. To some extent, it can be considered that measures with the capability to improve low back pain or sciatica have the potential to treat LDH [1]. In relative to the oral and surgical treatment of low back pain in LDH, acupuncture exhibits possible advantages in avoiding possible gastrointestinal adverse reactions of oral drugs and the secondary trauma of surgery. Meanwhile, existing systematic reviews [5, 6], meta analysis [7], and randomized controlled studies [8, 9] support that acupuncture has a good analgesic effect on low back pain. The Noninvasive Treatments for Acute, Subacute, and Chronic Low Back Pain: A Clinical Practice Guideline From the American College of Physicians [10] and the Chinese Expert Consensus on “Rehabilitation Treatment of Lumbar Disc Herniation” issued by the Skeletal Muscle Professional Committee of the Rehabilitation Physician Branch of the Chinese Medical Doctor Association [1] all recommend acupuncture as a therapeutic measure for low back pain. Therefore, acupuncture was selected as the control in this study.

China, India, Brazil, and other countries have rich traditional medicine resources [11, 12], but due to the lack of timely excavation and collation, many effective folk herbal medicines or technologies are on the verge of extinction. In recent years, China and India have taken the establishment of a defensive knowledge database of traditional medicine [13, 14] and the active release of protection lists [15] as the main means and methods to effectively protect and rationally develop folk medicine, which has promoted the sustainable development of folk medicine. Folk characteristic diagnosis and treatment technology is an important part of folk medicine, Ma’s bamboo-based medicinal moxibustion therapy is a characteristic folk diagnosis and treatment technology in China, belonging to the category of herb-partitioned-moxibustion. It has been applied for over 100 years and has accumulated rich clinical experience. Among them, it exhibits the most significant effect on treating low back pain in LDH, cold due to body deficiency and conditioning of chronic fatigue syndrome.

In our previous research, 14 LDH patients with low back pain were treated with Ma’s bamboo-based medicinal moxibustion. The clinical pre-trial found that 2 cases were clinically cured, 4 cases were markedly effective and 6 cases were improved. Besides, the post-treatment VAS score, ODI score, and M-JOA score were significantly lower than those before treatment (P<0.05). It suggests that this therapy has a certain application value clinically, which, however, lacks evidence-based evaluation. There is an absence of high-level clinical efficacy data, which restricts the real participation of the therapy in clinical decision-making and, hence, hinders its clinical popularization and application to a great extent.

Folk medicine resources are not only the medical characteristics of a country, but also the embodiment of a country’s cultural and economic characteristics. They are the unique areas of independent innovation of a country and a nation’s medicine. It is essential to actively explore and sort out folk medicine resources to protect their own and national medicine culture.

Thus, we designed this multi-center, randomized controlled trials to evaluate the clinical efficacy and safety of Ma’s bamboo-based medicinal moxibustion therapy in the treatment of LDH low back pain, in order to obtain evidence-based evidence that can be replicated and has high evidence level and to provide clinicians and patients with an appropriate technology that has evidence-based support for clinical efficacy and safety. At the same time, this study will be connected with China’s national intellectual property protection platform, and provide a reference for the establishment of an effective system of mining, sorting, screening, and evaluation of folk traditional Chinese medicine characteristic diagnosis and treatment technology at the national level, so as to promote the sustainable development and popularization and application of folk traditional Chinese medicine characteristic technology, constantly enrich the diagnosis and treatment technology and means of traditional Chinese medicine promote the development of the pharmaceutical industry and benefit the people.

### Study objectives

The objective of this randomized controlled trial is to evaluate the efficacy and safety of Ma’s bamboo-based medicinal moxibustion therapy in the treatment of patients with LDH low back pain. The specific objectives are (1) to evaluate the effectiveness of Ma’s bamboo-based medicinal moxibustion therapy in improving pain, lumbar dysfunction, daily living ability, and regulating of serum β-endorphin (β-EP) and serum substance P (SP) content in patients with LDH low back pain and (2) to evaluate the safety of this therapy by recording blood routine, liver and kidney function, electrocardiogram results, and the number, nature, and severity of adverse events.

## Methods

### Study design and setting

This is a parallel, non-inferiority, randomized controlled clinical trial aiming to compare the effect of Ma’s bamboo-based medicinal moxibustion therapy and regular acupuncture therapy on low back pain in LDH patients. The patients will be enrolled among outpatients and inpatients from the acupuncture departments of No.1 Affiliated Hospital of Guizhou University of Traditional Chinese Medicine, No.2 Affiliated Hospital of Guizhou University of Traditional Chinese medicine. Eligible patients will be randomly assigned to a Ma’s bamboo-based medicinal moxibustion therapy group and an acupuncture group in a 1:1 ratio. All items from the World Health Organization Trial Registration Data Set are shown in Table 1. The study flowchart is provided in Fig. 1. A Standard Protocol Items: Recommendations for Interventional Trials (SPIRIT) checklist and figure are provided respectively in Additional file 1 and Fig. 2.

**Table 1 Tab1:** All items from the World Health Organization Trial Registration Data Set (SPIRIT checklist, item 2b)

Data category	Information
Primary registry and trial identifying number	http://www.chictr.org.cn; ChiCTR2000038725
Date of registration in primary registry	29 September 2020
Secondary identifying numbers	-
Source(s) of monetary or material support	National Key Research and Development Project of China (2019YFC1708403)
Primary sponsor	Institute of Chinese Medical History and Literature, China Academy of Chinese Medical Sciences
Secondary sponsor(s)	-
Contact for public queries	[name]; [contact]
Contact for scientific queries	[name], Guizhou University of Traditional Chinese Medicine, [name], China.
Public title	Folk diagnosis and treatment technology in lumbar disc herniation study
Scientific title	Ma’s bamboo-based medicinal moxibustion therapy of low back pain in lumbar disc herniation: study protocol for a randomized controlled trial
Countries of recruitment	China
Health condition(s) or problem(s) studied	Lumbar disc herniation, low back pain
Intervention(s)	Ma’s bamboo-based medicinal moxibustion group
Key inclusion and exclusion criteria	***Inclusion criteria*** Patients who meet all of the following criteria will be enrolled in the trial: (1) patients who meet the above diagnostic criteria and pathological classification, with the lesion located in L3–S1; (2) patients aged 18–65 years, males or females; (3) patients with the course of disease ≥6 months; (4) drug users with drug withdrawal for 4 weeks, and non-drug users with discontinued treatment for 2 weeks; (5) patients with 3 ≤VAS scores ≤6; (6) willingness to sign written informed consent. ***Exclusion criteria*** Patients who meet any of the following criteria will be excluded from the trial: (1) patients with acute onset of low back pain in lumbar disc herniation; (2) patients with low back pain caused by other causes; (3) patients with other diseases requiring combined treatment using anti-inflammatory and analgesic drugs; (4) patients during pregnancy,lactation or pregnancy preparation; (5) patients with rash, skin damage, ulcers or other infectious diseases at the waist; (6) patients with serious diseases of the heart, liver, kidney,blood system, etc.; (7) patients with mental disorders or communication disorders who could not cooperate; (8) patients with high fever and yin deficiency.
Study type	Multicentre prospective randomized trial
Date of first enrolment	11 November 2020
Target sample size	312
Recruitment status	Recruiting
Primary outcome(s)	Visual analog scale (VAS)
Key secondary outcomes	Oswestry disability index (ODI); modified Japanese Orthopaedic low back pain (M-JOA) score; serum β-endorphin (β-EP); serum substance P (SP)

**Fig. 1 Fig1:**
[figure not shown]
Flow chart of the trial

**Fig. 2 Fig2:**
[figure not shown]
The SPIRIT figure. The schedule of enrollment, interventions, and assessments. VAS, visual analog scale; S-EP, β-endorphin; SP, substance P; ODI, Oswestry disability index; M-JOA, modified Japanese Orthopaedic Association low back pain score; ECG, electrocardiogram

The protocol has been approved by the ethical committee of No. 1 Affiliated Hospital of Guizhou University of Traditional Chinese Medicine (ethical approval number: k2020–039), and the study is registered at the Chinese Clinical Trial Registry, ChiCTR (registration number: ChiCTR2000038725; registration date: September 29, 2020).

### Patient and public participation

Participants and the public were not involved in the design or recruitment of this clinical trial. We will invite patients to be involved in the development of dissemination strategies.

### Eligibility criteria

#### Diagnostic criteria

The diagnostic criteria [2] are:Lower limb radiative pain, of which the pain location was consistent with the corresponding affected innervation areaLower limb sensory abnormalities, with decreased superficial sensation of the skin in the corresponding affected innervated areaPositive result of Lasegue test, Bragard test, Lasegue test of the unaffected side, or femoral nerve stretching testWeaker tendon reflex than that of the unaffected sideMuscle weaknessIntervertebral disc herniation indicated by lumbar MRI or CT, of which the nerve compression was consistent with the symptoms, signs of the affected nervesIn the first five criteria, patients could be diagnosed as LDH when meeting three of them combined with item 6

#### Pathological classification [16]

Intervertebral disc bulging, with an outward bulge of the annulus fibrosus of the whole intervertebral disc uniformlyLocalized herniation of the intervertebral disc, rupture of the inner layer of annulus fibrosus of the intervertebral disc, and partial herniation of nucleus pulposusIntervertebral disc herniation, rupture of most annulus fibrosus of the intervertebral disc, with intact outer annulus fibrosus merely, and the nucleus pulposus confined to the intervertebral discProlapse of the intervertebral disc, rupture of all annulus fibrosus of the intervertebral disc, nucleus pulposus tissue protruding out of the intervertebral disc and bound by the posterior longitudinal ligamentSequestered disc herniation, nucleus pulposus tissue protruding out of the annulus fibrosus and posterior longitudinal ligament, and sequestered in the spinal canal

Note: In this trial, patients with a pathological classification of intervertebral disc bulging, localized herniation of the intervertebral disc, and intervertebral disc herniation will be selected for experiment according to the long-term treatment experience and practice by using Ma’s bamboo-based medicinal moxibustion therapy.

#### Syndrome classification [17]

Low back pain due to cold-dampness evil

The presence of a history of suffering from cold in the waist, aggravation of symptoms when the weather changes or when there is cloudy, rainy, or cold weather, with severe cold and pain in the waist, accompanied by numbness or contracture that restricts the body movements of bending or raising up, even with pain involving the lower limbs2.Low back pain due to dampness-heat evil

Severe and heat pain in the waist, aggravation of symptoms in summer-heat and damp, cloudy and rainy weather, and possible alleviation after activities, accompanied by heavy body and feeling of sleepy, short voiding of reddish urine, yellow and greasy fur on the tongue, as well as soft and frequent pulse or wire and frequent pulse3.Low back pain due to static blood

The presence of a history of strain or old injury in the waist, aggravation of symptoms when getting up in the morning, tired and sitting for a long while, with stiffness of the muscles on both sides of the waist, pain like the stabbing of a needle, and pain in a fixed site4.Low back pain due to kidney deficiency

Major manifestations of soreness and weakness, with dull pain, alleviation when pressing and lifting, accompanied by weakness in legs and knees with relief when lying down and repeated onset, with fatigue and hypersomnia, and thready pulse as well

Note: In our study, patients with all the types based on the syndrome classification mentioned above will be included for experiment according to the long-term treatment experience and practice by using Ma’s bamboo-based medicinal moxibustion therapy.

#### Inclusion criteria

Patients who meet all of the following criteria will be enrolled in the trial:Patients who meet the above diagnostic criteria and pathological classification, with the lesion located in L3–S1Patients aged 18–65 years, males or femalesPatients with the course of disease ≥6 monthsDrug users with drug withdrawal for 4 weeks, and non-drug users with discontinued treatment for 2 weeksPatients with 3 ≤ VAS scores ≤6Willingness to sign written informed consent

#### Exclusion criteria

Patients who meet any of the following criteria will be excluded from the trial:Patients with acute onset of low back pain in lumbar disc herniationPatients with low back pain caused by other causesPatients with other diseases requiring combined treatment using anti-inflammatory and analgesic drugsPatients during pregnancy, lactation, or pregnancy preparationPatients with rash, skin damage, ulcers, or other infectious diseases at the waistPatients with serious diseases of the heart, liver, kidney, blood system, etc.Patients with mental disorders or communication disorders who could not cooperatePatients with high fever and Yin deficiency

#### Drop out criteria

Patients who meet any of the following criteria will be withdrawn:Occurrence of severe adverse eventsOther treatments received that could affect the outcomeVoluntary withdrawal for any reason

### Sample size calculation

The PASS software version 15.0 (NCSS, LLC. Kaysville, UT, USA.) was used to estimate the sample size. The trial is designed to determine the efficacy of Ma’s bamboo-based medicinal moxibustion therapy on low back pain in LDH and prove that its clinical efficacy is not inferior to normal acupuncture therapy. Therefore, we chose a non-inferiority trial design. According to the previous literature [8, 18] and the joint consideration of clinicians and statisticians, it is assumed that the standard deviation of VAS score reduction of patients using bamboo-based medicinal moxibustion is 2.0, the non-inferiority margin was set at 0.78, the significance level of the test is unilateral 0.05 and power of the test is 90%. According to the 1:1 grouping, the sample size required by each group was 140 cases, and the lost follow-up rate will be estimated at 10%. The final sample size of the treatment group and the control group was 156 cases respectively, and the total sample size was 312 cases.

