### Statistical analysis

Data analysis will be conducted in accordance with the intention-to-treat principle. Missing data will be handled using linear mixed effects models. Statisticians and chief investigators will work out an analysis plan and related forms before the database lock. The analysis will include case distribution, comparison of basic values, compliance, effectiveness, factors that influence efficacy, and safety. Subgroup analysis will be performed according to pathological classification and syndrome classification. Statistical analysis will be conducted using SAS 9.2 (SAS Institute Inc., Cary, NC, USA). The Wilcoxon rank-sum test, *t* test, or variance analysis will be performed for inter-group or intra-group comparison according to data distribution. The Wilcoxon rank-sum test will be used to compare ranked data. The chi-square test will be applied to compare enumeration data. All tests will be one-sided. A *p* value <0.05 will be considered statistically significant.

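### The stated inputs at one-sided 0.05 give about 114 patients per group, not 140; the 140 matches one-sided 0.025, so the sample size section and the decision rule need to be reconciled

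*Protocol article*

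**What the plan says.** The section *Sample size calculation* of the protocol article sets out a non-inferiority comparison: "Therefore, we chose a non-inferiority trial design". Its inputs are:

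- Variability: "the standard deviation of VAS score reduction of patients using bamboo-based medicinal moxibustion is 2.0". No separate SD is given for acupuncture.
- Margin: "the non-inferiority margin was set at 0.78".
- Error rates: "the significance level of the test is unilateral 0.05 and power of the test is 90" percent.
- Result: "According to the 1:1 grouping, the sample size required by each group was 140 cases".
- Attrition: "the lost follow-up rate will be estimated at 10" percent, leading to 156 per group and 312 in total.

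No expected true difference between the arms is stated.

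The section *Statistical analysis* sets the decision level: "All tests will be one-sided", with p below 0.05 as the threshold. The two sections therefore agree on one-sided 0.05.

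**The concern.** A reader who puts the stated inputs into the usual two-sample non-inferiority formula does not get 140. The gap is too large for rounding or for the choice between a normal and a t calculation, so at least one input is misstated or left out.

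The candidate that fits best is alpha, and alpha is also the pass/fail rule of the trial. If the trial was sized at one-sided 0.025 but is judged at one-sided 0.05, as the analysis section says, then the written rule is laxer than the one behind the sample size. Some results would count as non-inferior under one and not under the other. The claimed 90% power is also not the power at the stated alpha.

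**Working it through.** **Inputs.** From *Sample size calculation*: SD σ = 2.0, margin Δ = 0.78, power 90% (z = 1.2816), 1:1 allocation, 10% loss. Assumed, because the article does not state them: true difference 0, and SD 2.0 in the acupuncture arm as well.

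**Formula (normal approximation).** n per group = 2σ²(z_α + z_β)² / Δ². The t version takes the smallest n at which the noncentral t power reaches 90%.

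**Step 1: reproduce the plan's figure.** With one-sided 0.025 (z = 1.9600):

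- Normal: 2 × 4 × (1.9600 + 1.2816)² / 0.6084 = 138.2, so 139.
- t: 140.
- Attrition: 140 / 0.90 = 155.6, so 156 per group and 312 in total.

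All three published figures are matched.

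**Step 2: use the alpha as stated.** With one-sided 0.05 (z = 1.6449):

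- Normal: 2 × 4 × (1.6449 + 1.2816)² / 0.6084 = 112.6, so 113.
- t: 114.
- Attrition: 114 / 0.90 = 126.7, so 127 per group and 254 in total.

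The stated 140 exceeds 114 by 26, and 26 / 114 = 23%.

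**Step 3: power with 140 per group.** SE = 2.0 × √(2/140) = 0.239, and Δ/SE = 3.263.

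| One-sided alpha | Power, normal | Power, t |
|---|---|---|
| 0.05 | 94.7% | 94.6% |
| 0.025 | 90.4% | 90.2% |

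**Step 4: effect on the decision.** The largest observed deficit that still passes is Δ − t_α × SE on 278 degrees of freedom:

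- One-sided 0.05: 0.78 − 1.650 × 0.239 = 0.39 points.
- One-sided 0.025: 0.78 − 1.968 × 0.239 = 0.31 points.

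**Step 5: other routes to 140 at one-sided 0.05 and 90% power (normal formula).**

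- True deficit of 0.08: 2 × 4 × 8.564 / (0.78 − 0.08)² = 139.8, so 140.
- Acupuncture SD of 2.43, with 2.0 for moxibustion: (4 + 5.905) × 8.564 / 0.6084 = 139.4, so 140.
- Common SD of 2.23: 2 × 4.973 × 8.564 / 0.6084 = 140.0. This contradicts the stated 2.0.
- Rank-test inflation of 113: about 119 to 131, depending on the efficiency assumed. This does not reach 140.
- Equivalence by two one-sided tests: 142.3, so 143. This is close, but the design is stated as non-inferiority.

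**The case against.** The strongest reply is that two of the inputs used here are not in the document. The SD is stated for moxibustion only, and no expected difference is given. With a true deficit of about 0.08 or an acupuncture SD of about 2.43, one-sided 0.05, 90% power and 140 per group are all compatible, and a journal article may leave such an input to the full protocol. This stands. A reader might infer that alpha, power and sample size cannot all be true, or that the software was certainly run at 0.025. The article does not support either claim. The exact match at 0.025, reached by changing one input, makes that the likeliest explanation and no more.

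A second reply is that the two sections do not contradict each other on alpha. That also stands: both say one-sided 0.05, and the discrepancy is between that alpha and the 140.

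A third reply concerns the error rate. A reader might infer that testing at 0.05 carries more false non-inferiority risk than the sample size permits. Sample size does not set the type I error: a test at one-sided 0.05 carries the 5% risk that the protocol openly states, whatever the n. What survives is conditional. If 0.025 was the intended level, the written rule is laxer than intended.

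None of these replies removes the main point. The inputs as printed do not lead to the number as printed.

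**Conclusion.** The point holds as a failure of the stated inputs to yield the stated result. Given a true difference of 0 and equal SDs, both of which are assumptions, the requirement at one-sided 0.05 is 113 to 114 per group against 140 stated. The attrition step is correct.

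A reader might infer that the trial is too small. It is not: at the stated alpha it has more patients than the claimed 90% power needs.

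The consequence lies in how the result will be read. The power attached to the stated alpha is understated by about 4.6 percentage points. If the trial was in fact sized at 0.025, observed deficits between 0.31 and 0.39 points would be declared non-inferior under the written rule but not under the rule behind the sample size. Those two limits assume 140 evaluable patients per group and an observed SD of 2.0.

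Confidence is high that the figure does not reproduce, and lower as to the cause.

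**What to change.** Before database lock and unblinding, the sponsor should establish how 140 was obtained and bring *Sample size calculation* and *Statistical analysis* into line with it in one of three ways:

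1. State one-sided 0.025 in both sections, with non-inferiority concluded when the two-sided 95% confidence interval for the difference excludes a deficit of 0.78. The figures 140, 156 and 312 and the 90% power then stand. The downside is a stricter success threshold, at the power already claimed.
2. Keep one-sided 0.05 and restate the power as about 95% with 140 evaluable patients per group, giving the true difference and the acupuncture SD assumed.
3. Keep one-sided 0.05 and 90% power, and state the assumption that yields 140, such as the expected difference or the acupuncture SD.

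No option needs extra patients, and the text changes are short. They are still not mere wording. *Protocol amendments* says that analyses will not be modified after the first enrolment and requires ethics approval for significant changes, and *Trial status* puts the first enrolment in November 2020. The choice, above all option 1, should therefore go through a dated, documented amendment made without knowledge of results by group.
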